#### Secondary outcomes

The secondary outcomes are the following scales:

- CAESAR scale [38]: Experience of the patient’s dying and death (1 month after patient’s death). It determines the family member’s experience of EOL. There are three categories of responses:Difficult experience, low scores ≤59Moderate experience, scores ranging between 60 and 68Good experience, high scores ≥69

- QODD-1 – Quality of Dying and Death [39]: One question evaluating global satisfaction with the quality of dying and death (1 month after patient’s death)

- MISS-21 – Medical Interview Satisfaction Scale – the Rapport Subscale only (1 month after the patient’s death) [40]

- HADS – Hospital Anxiety and Depression Scale [41] (1, 3, and 6 months after the patient’s death): There are two subscales, anxiety and depression. Scores for each subscale range from 0 to 21, categorized as follows:normal 0–7mild 8–10moderate to severe 11–21

Scores for the entire scale (emotional distress) range from 0 to 42, with higher scores indicating more distress.

- IES-R – Impact of Event Scale, Revised [42]: Risk of presenting with PTSD symptoms (3 and 6 months after the patient’s death). It assesses the subjective distress caused by traumatic events. The total score ranges from 0 to 88. There are three categories of risk:Low risk, scores ranging between 1 and 11Moderate risk, scores ranging between 12 and 32High risk, scores of 33 and over

#### Exploratory measures

The following are also measured:Questionnaire (developed by the Famiréa group) for relatives about lifestyle disruptions (6 months)Qualitative semi-structured interviews with family members (9 months)Strategy checklist to assess adherence to the intervention (intervention centers only)Questionnaire for physicians and nurses in the intervention group to evaluate the communication strategy

In each center, the local investigator will complete an ICU characteristics form.

### Statistical analysis

The hypothesis is that the proactive communication strategy will decrease the proportion of relatives presenting complicated grief symptoms from 50% to 35% 6 months after the patient’s death (assumed decrease). To do so, we need to recruit 454 relatives (227 in each group) to give a power of 90% and a type I error rate α of 0.05. Moreover, given it is a cluster randomized trial, a between-cluster variation must be accounted for, using an inflation factor or design effect of $$ 1+\left(\overline{n}-1\right)\uprho $$, where $$ \overline{n} $$ is the average cluster size and ρ is the intracluster correlation coefficient assuming the clusters are of a similar size [43]. Assuming a small clustering effect (intracluster correlation coefficient = 0.05), with an estimated average recruitment of 25 subjects per cluster, the inflation factor is set at 1.55, resulting in 704 enrolled subjects. As it is expected that 25% of the relatives will be lost to follow-up at 6 months [1, 4, 21], the sample size is increased to 874 (437 in each group).

The analysis will be done according to the intention-to-treat principle (each subject will be analyzed in the group to which they were was assigned by the randomization, regardless of whether or not it was effectively done). Descriptive statistics in each group (means, medians, or percentages as appropriate) will be used to assess any marked differences between the intervention and control groups. Point estimates with 95% confidence intervals will be reported for the primary outcome. This is a cluster randomized controlled trial, with correlation among patients from the same cluster.

The primary and secondary outcomes will be compared across randomized groups at the individual patient level, taking into account the correlation induced by the study design. The intracluster correlation coefficient or *k* statistic for each primary and secondary outcome will provide an indication of the extent of the clustering. Moreover, the correlation will be considered in the statistical analysis of the outcomes using mixed effects models, with both adjusted and unadjusted estimates [43, 44].

Missing data on covariates will use the multiple imputation by chained equation. The scores will be analyzed based on original data, and when available, according to established cutoffs. All tests will be bilateral and significance will be defined as *p* < 0.05.

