#### Randomization

Participating centers are assigned by simple random allocation to one of the two groups in a 1:1 ratio. Each subject is treated according to the strategy allocated to the center (Fig. 2). The randomization between the two parallel groups of centers was centrally generated by a statistician not involved in the study using permuted and balanced blocks of non-released size. Randomization is stratified using recruitment period, and also on centers’ previous participation in Famiréa studies (experienced vs. new centers).

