### Provisional timetable

Altogether, 36 centers (Additional file 1) are participating in the study. Based on the CAESAR study [1], four or five decisions to withhold or withdraw life-sustaining therapies are managed per month by each ICU. Each ICU will recruit 25 relatives. To permit a quality follow-up of the relatives and to avoid researchers being overloaded with follow-up telephone calls, relatives are enrolled in three time periods: centers 1 to 12 recruit during the first 6 months, centers 13 to 25 start during the next 6 months, and centers 26 to 36 during the final 6 months. Hence, recruitment is expected to last approximately 18 months. The follow-up of relatives will last for a total of 24 months.

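### The design effect is given as 1.55, but the protocol's own formula with 25 relatives per center and an ICC of 0.05 gives 2.20, so the planned size does not provide the stated 90% power at that ICC

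*Protocol article*

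**What the plan says.** The sample size paragraph (Protocol article, Statistical analysis) targets a fall in the primary event; the strategy is expected to "decrease the proportion of relatives presenting complicated grief symptoms from 50% to 35% 6 months after the patient’s death". Before clustering, the requirement is stated as "we need to recruit 454 relatives (227 in each group) to give a power of 90% and a type I error rate α of 0.05". Tests are two-sided ("All tests will be bilateral and significance will be defined as" p < 0.05).

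The article then gives the inflation factor as 1 + (n − 1)ρ, where n is the average cluster size and ρ the intracluster correlation. The ICC is fixed in words and number: "Assuming a small clustering effect (intracluster correlation coefficient = 0.05"). The same sentence continues: "with an estimated average recruitment of 25 subjects per cluster, the inflation factor is set at 1.55, resulting in 704 enrolled subjects". For an expected 25% loss to follow-up at 6 months, the total is raised to 874 (437 per group).

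The cluster size is repeated elsewhere. The Abstract gives 36 centers with 25 relatives each, and Provisional timetable says "Each ICU will recruit 25 relatives". No section gives a smaller cluster size or a smaller ICC.

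**The concern.** The formula, its two inputs and its result stand together in the text, and the result does not follow from the inputs. The figure of 704 is the product of 454 and 1.55, so this is not an isolated misprint: the sample size was built on the wrong factor.

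The stated 90% power for a 15-point reduction in prolonged grief is the justification for the trial's size. If the true ICC is near the assumed 0.05, the design is weaker than its readers are told. A null result would then be taken as firmer evidence against a 15-point benefit than it is. Anyone reusing the calculation for another cluster trial would also undersize it.

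**Working it through.** **Inputs, all from the protocol article.** Event rates 0.50 and 0.35; two-sided α = 0.05; power 90%; ICC 0.05; 25 relatives per center; 36 centers; 25% loss; stated factor 1.55; stated totals 454, 704 and 874.

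**1. The base size reproduces.** With mean proportion 0.425 and the pooled formula:

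n per group = [1.960·√(2 × 0.425 × 0.575) + 1.2816·√(0.25 + 0.2275)]² / 0.15² = 226.2, rounded up to 227. The total is 454, as stated.

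**2. The design effect does not reproduce.**

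| Reading | Calculation | Design effect |
|---|---|---|
| As stated, 25 per center | 1 + 24 × 0.05 | 2.20 |
| Net of 25% loss, 18.75 per center | 1 + 17.75 × 0.05 | 1.8875 |
| Stated in the article | – | 1.55 |

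Working backwards, 1.55 needs a cluster size of 1 + 0.55/0.05 = 12 at ICC 0.05, an ICC of 0.55/24 = 0.0229 at 25 per center, or an ICC of 0.55/17.75 = 0.031 at 18.75 per center.

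**3. The number needed for analysis.** 454 × 1.55 = 703.7, which is the stated 704. With the correct factor it is 454 × 2.20 = 999, or 454 × 1.8875 = 857 if cluster size is counted after loss.

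**4. Power of the actual design at ICC 0.05.** Enrolled: 36 × 25 = 900. Analysed: 900 × 0.75 = 675, or 18.75 per center. Effective n per arm = 675 / 1.8875 / 2 = 178.8.

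Power = Φ{[0.15 − 1.960·√(0.48875/178.8)] / √(0.4775/178.8)} = Φ{(0.15 − 0.1025)/0.0517} = Φ(0.92) ≈ 0.82.

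With a t reference on 36 − 2 = 34 degrees of freedom it is about 0.80.

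| Scenario at ICC 0.05 | Analysed | Design effect | Power |
|---|---|---|---|
| 900 enrolled, 25% lost | 675 | 1.8875 | 82% |
| 874 enrolled, 25% lost (18.2 per center) | 655.5 | 1.86 | 81.5% |
| 900 enrolled, factor for 25 per center kept | 675 | 2.20 | 76% |
| 900 enrolled, nobody lost | 900 | 2.20 | 87% |

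The third row is a pessimistic bound, because it applies the factor for 25 per center to centers that contribute 18.75. The first row is the consistent one.

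**5. Detectable effect.** With 178.8 effective relatives per arm, 90% power is reached at about 50% versus 33%, a difference of about 17 points.

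**6. Sensitivity to the ICC** (675 analysed, 18.75 per center, normal reference): about 92% at 0.023, 82% at 0.05 and 72% at 0.08.

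**7. The step from 704 to 874.** Allowing for 25% loss, 704/0.75 = 939. Multiplying instead, 704 × 1.25 = 880. The stated 874 covers a loss of only 1 − 704/874 = 19.5%. If 1.55 is taken at face value and applied to the 655.5 left from 874, power is about 88%.

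**The case against.** The strongest reply is that the text shows three numbers (25, 0.05 and 1.55) to be mutually inconsistent but does not show which is wrong. If the ICC behind 1.55 was really about 0.023, the 36 × 25 design has about 92% power and the headline claim survives. That stands as a condition on the conclusion. It does not remove the error, because 0.05 is what the article states and describes, and in that case the printed ICC would need correcting and the smaller value justifying.

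A second reply is that the fault lies in planning and not in validity. The analysis uses mixed effects models that account for clustering, the ICC will be reported, and the primary outcome will carry a 95% confidence interval, so a careful reader of a null result can see its precision. This is fair and limits the harm: the inference does not depend on 1.55. The stated power is still wrong at the stated ICC.

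A third point is that 76% mixes two cluster sizes. It is shown above only as a bound; the shortfall to quote is 90% against about 80–82%.

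Finally, 874 does not follow from 704 at 25% loss, so correcting the inflation factor alone would not repair the whole chain. That is correct, and it adds to the problem.

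The fact that an article condenses a fuller protocol does not help here. Nothing is missing: the formula, the inputs and an incompatible result are all printed.

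**Conclusion.** The concern holds. The stated formula and inputs give a design effect of 2.20, or 1.89 on the most favourable reading, and not 1.55. Under the stated ICC of 0.05, 25% loss and similar center sizes, the 36 × 25 design has about 82% power, or about 80% allowing for 36 clusters. The 874 target gives about 81–82%. The type II error is therefore 18–20% instead of 10%. Even with no loss at all, 900 relatives would give about 87%, so 90% is not reached at this ICC.

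The power shortfall depends on 0.05 being the intended ICC. The contradiction between the printed numbers does not depend on it.

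**What to change.** First establish which number is wrong: the ICC, the cluster size or the factor.

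- **If the ICC of 0.05 stands:** replace 1.55 with 2.20 (25 analysed per center) or 1.89 (18.75 analysed per center), correct the figures that follow from it, and restate the power of the 36 × 25 design as about 80–82% with 25% loss.
- **If 1.55 was intended:** state the ICC it implies at 25 per center (about 0.023) and justify it.
- **In either case:** reconcile 874 with the 25% loss assumption, and add a short table of power for ICCs from 0.02 to 0.08, so that the dependence on this assumption is visible before the results are known.

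The cost is wording in the protocol or analysis plan and, if 0.05 stands, a less favourable stated power. No additional centers or relatives are required, and the correction can be made while recruitment continues.

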**Methods/design:**

The COSMIC-EOL trial is a prospective, multicenter, cluster randomized controlled trial in which centers are allocated to two parallel arms: (1) intervention centers where relatives benefit from three-step physician-driven support during the dying and death process and (2) control centers where, during the dying and death process, relatives receive the standard of care practice. Each of the 36 participating centers will include 25 relatives of patients with a length of stay ≥2 days. Participating relatives will be followed up by phone at 1, 3, and 6 months after the patient’s death to complete questionnaires permitting evaluation of their post-ICU burden. The main outcome is prolonged grief measured 6 months after the death using the PG-13. Other outcomes include evaluation of quality of dying, quality of communication, anxiety, depression, and post-traumatic stress. The estimated duration of the study is 36 months.

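### The allowance for 25% loss to follow-up is miscalculated: 704 evaluable relatives require 939 enrolled, not 874

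*Protocol article*

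**What the plan says.** The Statistical analysis section builds the sample size in three steps.

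1. The intervention is assumed to "decrease the proportion of relatives presenting complicated grief symptoms from 50% to 35% 6 months after the patient’s death". For this, "we need to recruit 454 relatives (227 in each group") "to give a power of 90% and a type I error rate α of 0.05".
2. An inflation factor of 1.55 for clustering raises 454 to 704.
3. An allowance for attrition follows: "As it is expected that 25% of the relatives will be lost to follow-up at 6 months", "the sample size is increased to 874 (437 in each group").

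Tests are two-sided ("All tests will be bilateral and significance will be defined as" p < 0.05), and centers are "assigned by simple random allocation to one of the two groups in a 1:1 ratio". The abstract gives the recruitment plan: "Each of the 36 participating centers will include 25 relatives". The Provisional timetable repeats 36 centers and 25 relatives per ICU, which makes 900.

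**The concern.** The article prints the starting number (704), the expected loss (25%) and the result (874), and the three do not agree. Although 704 is described as a number enrolled, it is then raised because relatives will be lost, so it serves as the number needed with a 6-month outcome. The primary outcome is the PG-13, completed 6 months after the death in a telephone follow-up, so a relative lost by then contributes no primary outcome. Multiple imputation is stated for covariates only.

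The stated 90% power for the primary outcome is therefore at stake. A sponsor who stops at 874 would believe the trial is protected against 25% attrition when it is not. Readers would also use 874 to judge how informative a null result is.

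**Working it through.** **Inputs (all from Statistical analysis unless noted).** Proportions 0.50 and 0.35; two-sided α = 0.05; power 0.90; 1:1 allocation (Randomization); inflation factor 1.55; intracluster correlation (ICC) 0.05; average cluster size 25; loss 25%; 36 centers × 25 relatives (abstract, Provisional timetable).

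**Step 1, individual randomization.** Normal approximation with pooled variance under the null, no continuity correction:

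n per group = [1.960·√(2 × 0.425 × 0.575) + 1.282·√(0.50 × 0.50 + 0.35 × 0.65)]² / 0.15² = 226.2, rounded up to 227, total 454. The plan's figure is reproduced.

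**Step 2, clustering with the plan's factor.** 454 × 1.55 = 703.7, rounded to 704. Reproduced.

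**Step 3, attrition.**

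- Correct conversion: 704/(1 − 0.25) = 938.7, so 939 (940 if the groups are equal).
- Common shortcut: 704 × 1.25 = 880.
- Stated: 874. Neither formula gives it.
- Loss that 874 covers: 1 − 704/874 = 19.5%.
- Evaluable at 25% loss: 874 × 0.75 = 655.5, which is 704 − 655.5 = 48.5 short (7%).
- Evaluable from the operational plan: 36 × 25 = 900, and 900 × 0.75 = 675, which is 29 short.

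**Power.** Effective n = evaluable number / design effect, put into the same two-proportion formula. Three design effects are shown because the 1.55 does not follow from the plan's own inputs:

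- 1.55, as stated;
- 1 + (18.75 − 1) × 0.05 = 1.89, using the stated ICC and the evaluable cluster size, 25 × 0.75 = 18.75;
- 1 + (25 − 1) × 0.05 = 2.20, using the stated ICC and the stated cluster size.

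| Enrolled | Evaluable at 25% loss | Power, 1.55 | Power, 1.89 | Power, 2.20 |
|---|---|---|---|---|
| 874 | 655.5 | 88.0% | 81.0% | 74.7% |
| 900 | 675 | 88.9% | 82.1% | 76.0% |
| 939 | 704.25 | 90.1% | 83.7% | 77.7% |

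The 1.55 column isolates the attrition step: 939 restores 90%, while 874 and 900 do not. The gap between that column and the other two comes from the design effect, a separate error.

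**The case against.** The strongest reply is about size and remedy, since the division itself is not in doubt.

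- **The effect is small.** With 1.55 held, the shortfall is 2.0 points at 874 and 1.1 points at the 900 that centers are asked to recruit. No hypothesis, endpoint or analysis changes. This stands, and the attrition step should not be credited with the larger losses in the other two columns.
- **Attrition also shrinks clusters.** If 1.55 is taken as right for clusters of 25, the implied ICC is 0.55/24 = 0.023. With 18.75 evaluable per cluster the design effect becomes 1 + 17.75 × 0.023 = 1.41, the effective n at 874 is 655.5/1.41 = 466, and power is 90.8% (91.6% at 900). The arithmetic is right, but it needs an ICC of 0.023, and the plan states 0.05. With the stated ICC the same argument gives 81.0% at 874 and 82.1% at 900. The rescue therefore fails on the plan's own inputs. It does show that the power consequence of this step cannot be fully separated from the design effect, even though the division can.
- **874 may be a rounding of the shortcut.** 454 × 1.54 × 1.25 = 873.95, so the figure may come from multiplying by 1.25 with a slightly different factor. This is conjecture, and multiplying by 1.25 would still be the wrong conversion for 25% loss.
- **939 is not usable as it stands.** It exceeds the planned 900 and rests on 704, which is itself doubtful. This stands and shapes the fix.

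**Conclusion.** The concern holds. From the plan's own 704 and 25% loss the enrolment target should be 939. The stated 874 protects against 19.5% loss only and misses the plan's own evaluable number by about 48 relatives (7%). Recruiting the full 900 still misses it by 29. No other section repairs the figure.

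With 1.55 held, power is 88.0% to 88.9% instead of 90%, so the isolated effect is about 1 to 2 points. With the stated ICC of 0.05 it is about 81% to 82% (18.75 evaluable per cluster) or 75% to 76% (25 per cluster), mostly because of the design effect. The shortfall appears on every reading that keeps the plan's stated inputs. These figures assume equal groups, equal cluster sizes, loss of exactly 25% in both arms and the normal approximation that reproduces 454. The correction is needed because a headline number for the primary outcome is wrong, even though this step alone does modest damage.

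**What to change.** Correct the sample-size chain once, with the design effect settled first and the attrition step then computed as N/(1 − 0.25). There are two ways to do this.

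1. **Keep enrolment at 36 × 25 = 900.** Remove 874, state 675 expected evaluable relatives, and give the power that follows from the design effect the sponsor can defend: 88.9% at 1.55, 82.1% at 1.89 or 76.0% at 2.20. This costs wording and a less favourable stated power, with no extra enrolment.
2. **Keep 90% power and change the target.** With 1.55 the target is 939. With the stated ICC it is 454 × 1.8875/0.75 = 1,143 (18.75 evaluable per cluster), or 454 × 2.2 = 999 evaluable and 999/0.75 = 1,332 enrolled (25 per cluster). All three exceed the planned 900. The last two keep cluster size fixed, so they imply more centers. This option costs real recruitment.

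Replacing 874 by 939 while leaving 1.55 untouched would repair one step of a chain that is still wrong. Whichever option is chosen, the target in Statistical analysis and the 36 × 25 in the abstract and Provisional timetable should agree, and 704 should be described as the number with 6-month outcome data.

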**Fig. 2 Fig2:**
[figure not shown]
Study design

Relatives are included after the decision to withhold or withdraw treatment has been made using a signed consent form approved by the institutional review board. Relatives who consent to participate are contacted by phone three times: 1, 3, and 6 months after the patient’s death. All telephone calls are done by trained sociologists and psychologists from the Famiréa group. Telephone interviewers are blinded (control vs. intervention). The estimated duration of each call 1, 3, and 6 months after the patient’s death is 40 min, 30 min, and 30 min, respectively.

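### The randomisation strata are not stated to be in the primary model, and neither the adjusted nor the unadjusted estimate is named as primary

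*Protocol article*

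**What the plan says.** The Randomization section of the protocol article states that "Randomization is stratified using recruitment period" and, as a second factor, on whether the centre had taken part in Famiréa studies before. Allocation within strata uses permuted, balanced blocks. The same section opens by saying that "Participating centers are assigned by simple random allocation to one of the two groups in a 1:1 ratio", which is at odds with blocks and strata, although the later sentences make the actual method clear.

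The Statistical analysis section says that outcomes will be compared "taking into account the correlation induced by the study design", "using mixed effects models, with both adjusted and unadjusted estimates". It mentions covariates only when it says how their missing values will be imputed. Neither that section nor Additional analyses names recruitment period or Famiréa experience. Additional analyses does announce a test of the centre effect and three interactions (spouse, French descent, age over 65), but none of these is adjustment for a randomisation stratum. No sentence says which of the two estimates is the primary result.

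**The concern.** Stratified allocation balances the arms on the strata. If the strata are prognostic, the treatment difference then varies less from one possible allocation to another than it would under unrestricted allocation. An analysis that leaves the strata out does not see this. It counts the differences between strata as noise between centres, so its standard error is too large, its interval too wide and its test conservative.

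Famiréa experience could well be prognostic. The Eligibility criteria section describes the network's ICUs as striving to apply published findings on family-centred care, which is close to the mechanism under test.

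The second problem is the missing ranking. Two estimates are announced for the primary outcome. If they fall on opposite sides of the 5% threshold, the protocol does not say which one decides the trial.

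**Working it through.** **Inputs from the protocol.** 36 centres of 25 relatives; 25% lost to follow-up, leaving 25 × 0.75 = 18.75 evaluable per centre; intracluster correlation (ICC) 0.05; 50% against 35%; two-sided alpha 0.05. There are three recruitment periods (12, 13 and 11 centres) and two experience levels, so six strata.

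**Assumptions.** The share R² of between-centre variance that the strata explain is not in the protocol, so a range is shown. The number of experienced centres is not given either. Six equal strata of six centres, allocated 3:3, are assumed; the real periods cannot match this exactly.

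**The plan's own figure.** With pooled variance and no continuity correction, n per group = [1.96 × √(2 × 0.425 × 0.575) + 1.282 × √(0.50 × 0.50 + 0.35 × 0.65)]² / 0.15² = 226.2, rounded up to 227, or 454 in total. This matches the protocol, so the effect size and error rates are read correctly. Nothing in this point changes that number.

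**Why the unadjusted test is conservative.** In units of the individual-level variance, a centre mean has variance 0.05 + 0.95/18.75 = 0.1007, which is roughly what the unadjusted analysis estimates. With arms balanced within strata, the part that actually affects the treatment difference is 0.05 × (1 − R²) + 0.95/18.75:

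- R² = 20%: 0.0907, or 90% of 0.1007. The effective critical value is 2.03/√0.90 = 2.14, and the type I error on 34 degrees of freedom is about 0.039.
- R² = 40%: 0.0807, or 80% of 0.1007. The effective critical value is 2.03/√0.80 = 2.27, and the type I error is about 0.030.

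**Simulation.** Centre-level analyses of 36 centres were simulated under these assumptions, with and without the six strata in the model, as a stand-in for the mixed model.

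| Share explained by strata | Type I error, unadjusted | Type I error, strata in model | Power, unadjusted | Power, strata in model |
|---|---|---|---|---|
| 0% | about 0.05 | about 0.05 | 0.80 | 0.79 |
| 20% | about 0.04 | about 0.05 | 0.81 | 0.83 |
| 40% | 0.033 | about 0.05 | 0.83 | 0.87 |

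Independent runs agree to within about a point of power. The simulated type I error at 40% is a little above the hand figure because six strata contribute slightly less than their full variance to the pooled estimate. Wider shares continue the trend: at 50% and 75%, the unadjusted type I error is 0.029 and 0.020, and power is 0.84 against 0.89 and 0.86 against 0.94.

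**Choosing between the two results.** With shares from 0% to 75%, the two analyses disagree on significance in about 1% to 3% of trials under the null and 2% to 8% under the planned effect. If either could be claimed, and adjusted means adjusted for the strata only, type I error is 0.051 to 0.054. If the covariate set is open, the protocol gives no basis for a bound.

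**Why power starts near 80% and not 90%.** With ICC 0.05 and 18.75 evaluable per centre, the design effect is 1 + 17.75 × 0.05 = 1.89. The protocol's factor of 1.55 does not follow from its own inputs, since 1 + 24 × 0.05 = 2.20. That is a separate matter and does not affect the comparison between columns.

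**The case against.** The strongest reply is that this is an argument from silence. The protocol says adjusted without defining it, so the strata may well be in the adjusted model. A covariate list is commonly left to the analysis plan, which is not shown. That stands: a reader might infer that the analysis ignores the strata, and the protocol does not say so. What remains is that an unadjusted estimate is announced on equal terms, with no primary named.

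It is also fair that the error is in the safe direction and that its size rests on an assumed R², which could be zero.

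Several stronger readings are tempting but not supported:

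- A reader might take the 90% and 80% ratios as a 10% to 20% cut in the variance of the effect from adjustment, and so expect a larger gain in power. Under balanced strata the two centre-level estimates coincide. Stratified allocation has already removed that variance, and only the reported standard error differs.
- A reader might add inflation from using a normal reference with only 36 centres. The protocol states no reference distribution.
- Descriptive statistics "will be used to assess any marked differences between the intervention and control groups". This could be read as a rule for choosing covariates by observed imbalance, but nothing links it to covariate selection.
- "Relatives are included after the decision to withhold or withdraw treatment has been made using a signed consent form" fixes the timing relative to the treatment decision. It does not say that staff know the centre's allocation. Such knowledge can be inferred from the training of intervention teams before recruitment, but selective enrolment is a different issue, and modelling the strata would not cure it.
- The word simple does not show that allocation was unstratified, since the same section goes on to specify blocks and strata.

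**Conclusion.** The point holds in limited form. The protocol stratifies centres on two factors, does not state that they enter the model, and ranks neither of its two estimates. If the strata explain 20% to 40% of between-centre variance, an unadjusted primary result would have a type I error of about 3% to 4% and give up about 2 to 5 points of power. If they explain none, the difference is negligible. These sizes rest on the assumed R², ICC 0.05, equal strata with 3:3 allocation, and a centre-level stand-in for the mixed model. The consequence is a conservative test and an open choice of primary result. It is not a materially inflated error rate, provided that adjusted means adjusted for the strata. The change is worth making because it is nearly free.

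**What to change.** State in the Statistical analysis section that the primary analysis of PG-13 at 6 months is the mixed model with a random centre effect and fixed effects for recruitment period and Famiréa experience. State that the unadjusted estimate is supportive. If the analysis plan already says this, the protocol needs only to agree with it.

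The cost is a few between-centre degrees of freedom. Main effects for three periods and two experience levels use 2 + 1 = 3, taking 34 to 31. All six strata would use 5, leaving 29 and moving the critical value only from 2.03 to 2.05. Sample size and data collection are unchanged.

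As an editorial correction only, delete the word simple from the first sentence of the Randomization section so that it agrees with the stratified blocks described there.

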#### Outcomes

Outcomes are at the individual patient level. The primary outcome is the Prolonged Grief 13-item questionnaire (PG-13) [37], completed 6 months after the patient’s death. The PG-13 measures five criteria for prolonged grief disorder: event (bereavement); separation distress; duration (i.e., >6 months since the bereavement); cognitive, emotional, and behavioral symptoms; and social or occupational impairment. The score range is 11–55 and a score of 36 or more is a clinical indicator of prolonged grief disorder. In addition, all five criteria must be met.

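### The stated multiple imputation covers covariates only, so the 25% of relatives expected to lack the 6-month PG-13 would most likely not contribute to the primary comparison

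*Protocol article*

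**What the plan says.** All references are to the protocol article.

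- **Missing-data rule (Statistical analysis).** "Missing data on covariates will use the multiple imputation by chained equation". No rule for a missing outcome is given.
- **Expected loss (Statistical analysis).** The last step of the sample-size calculation reads "As it is expected that 25% of the relatives will be lost to follow-up at 6 months", and the total is raised to 874 (437 per arm).
- **Primary outcome (Outcomes).** PG-13, "completed 6 months after the patient’s death". No earlier PG-13 is scheduled.
- **Earlier scores (Secondary outcomes).** CAESAR is collected at 1 month and IES-R at 3 and 6 months. HADS is collected three times: "HADS – Hospital Anxiety and Depression Scale [41] (1, 3, and 6 months" after the death.
- **Model (Statistical analysis).** Correlation within centres is handled "using mixed effects models, with both adjusted and unadjusted estimates".
- **Analysis principle (Statistical analysis).** "The analysis will be done according to the intention-to-treat principle", explained as "each subject will be analyzed in the group to which they were was assigned by the randomization".

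**The concern.** The only imputation that the article names is directed at covariates, while the variable it expects to be missing in one relative out of four is the primary outcome. A mixed model with a centre effect does not help here. Each relative has a single PG-13 value, so a relative without it supplies no outcome to the model.

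Two things are at stake. First, the primary comparison would rest on about three quarters of the enrolled relatives. If the reasons for missing the 6-month call are linked to distress, and linked differently in the two arms, the comparison is biased. Differential loss is conceivable: the intervention aims to change distress, and its third step offers relatives the option of contacting the team during bereavement (Table 1). Second, many relatives lost between the first and last call will already have HADS, CAESAR or IES-R scores, which may carry information about their grief. The stated rule makes no use of them for the primary outcome.

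**Working it through.** **1. The plan's own figures.** Two-sided alpha 0.05, 90% power, 50% vs 35%: 227 per arm, 454 in total, which reproduces. 454 × 1.55 = 703.7, giving 704, which also reproduces. The step from 704 to 874 for 25% loss does not reproduce exactly: 704 × 1.25 = 880 and 704 / 0.75 = 939. That is a separate matter, and nothing below depends on it.

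**2. Number without a primary outcome.** 0.25 × 874 = 218.5, or about 109 per arm, leaving about 656. With 36 centres × 25 = 900 relatives, 225 are missing and 675 remain.

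**3. What the missing quarter can do to the estimate.** With 25% missing in each arm:

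difference in all enrolled = 0.75 × (difference in observed) + 0.25 × (difference in missing)

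Suppose the observed relatives show the planned 50% vs 35%, a 15-point difference. The values for the missing are assumed:

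| Missing, control vs intervention | Difference in all enrolled |
|---|---|
| 50% vs 35% | 0.75 × 15 + 0.25 × 15 = 15.0 |
| 50% vs 50% | 0.75 × 15 + 0.25 × 0 = 11.3 |
| 50% vs 70% | 0.75 × 15 + 0.25 × (−20) = 6.3 |

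**4. Bias under an explicit drop-out model.** All inputs are assumptions except the 25% loss and the 50% prevalence. Early distress a is standard normal. Grief is present if y = ρa + √(1−ρ²)·e exceeds 0; with ρ = 0.6 this is y = 0.6a + 0.8e. Drop-out is logistic in a with slope b per SD, and the intercept is set so that 25% are lost in each arm. There is no true effect. Bias is the absolute difference between arms among those observed.

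| Slopes b in the two arms | ρ | Bias (points) |
|---|---|---|
| Equal in both arms | 0.6 | 0.0 to 0.1 |
| 0.5 vs 0.3; 0.8 vs 0.5 | 0.6 | 1.1 to 1.4 |
| 0.3, 0.5 or 0.8 in one arm, 0 in the other | 0.6 | 1.8, 2.9, 4.3 |
| 0.3 to 0.8 in one arm, 0 in the other | 0.3 | about 1 to 2 |
| +0.5 vs −0.5 | 0.6 | 5.6 to 5.8 |

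With equal slopes and a true 15-point effect, the observed difference is 14.8 to 14.9. Weighting by the inverse probability of being observed, given a, brings the bias below 0.1 point. That happens because drop-out in this model depends only on a and a is known for everyone. Imputation that uses the early scores relies on the same condition.

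**5. Scale.** With 656 evaluable relatives, the 95% half-width for 50% vs 35% is 1.96 × √[(0.25 + 0.2275)/n], where n = 874 × 0.75 / 2 / design effect. At the printed design effect of 1.55, n = 211.5 and the half-width is 9.3 points. At 1 + 24 × 0.05 = 2.20, which the article's formula gives, n = 149.0 and the half-width is 11.1 points. A bias of 1 to 4 points is smaller than the random error but not negligible against a 15-point target.

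**The case against.** The strongest objection is that this is a condensed article whose analysis plan is not shown. Outcome imputation and sensitivity analyses are often settled there, and a sentence about covariates does not forbid imputing outcomes. This stands in part: exclusion of relatives without PG-13 is an inference. What keeps the point alive is that the article is not merely silent. It fixes a rule, confines it to covariates, and does so beside its own forecast of 25% loss on the outcome.

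A reader might infer more than the article supports:

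- **That intention-to-treat is violated.** The article defines it by the arm assigned, whether or not the strategy was delivered. Missing scores do not breach that definition. They only mean that not all enrolled relatives are included.
- **That the article rules out imputed outcomes.** The sentence "The scores will be analyzed based on original data" goes on to mention established cut-offs, so its contrast is raw scores against categories, not observed against imputed values. Enlarging the sample for loss is also compatible with later imputation.
- **That the imputation ignores centre.** The article does not say whether it is single-level or multilevel.
- **That bias is likely.** It requires drop-out that differs by arm. The same blinded interviewers call both arms, and the article gives no evidence of differential loss.
- **That the early scores are strong predictors, or that few covariates will be missing.** The article gives no figure for either.

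The article also does not say when the 25% are lost. Those gone before the first call have no early scores, and imputation would gain little for them.

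**Conclusion.** The point holds as an improvement to a stated rule that is poorly placed. It is neither an error of fact nor a breach of the article's intention-to-treat definition. Read as written, about 218 of 874 relatives would most likely not enter the primary comparison, and the earlier scores of those lost later would go unused.

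The possible bias runs from about 0 points (drop-out equally related to distress in both arms), through about 1 to 4 points (unequal strength or one arm only, assumed correlation 0.3 to 0.6), to about 6 points (opposite directions). These figures depend on the assumed correlation and drop-out slopes. The article can fix neither the direction nor the size. Confidence is moderate, because the exclusion is inferred and an unseen analysis plan may already deal with it.

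**What to change.** State how a missing 6-month PG-13 is handled, and extend the planned multiple imputation to it:

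- Impute separately by arm, in a way that respects centre.
- Include 1- and 3-month HADS, 3-month IES-R, 1-month CAESAR and the randomisation strata (recruitment period, previous Famiréa participation).
- Report the complete-case result alongside.
- Add a delta-adjusted analysis in which the imputed scores are shifted by arm, to show how far they must move before the conclusion changes.

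The cost is analysis-plan wording and modest programming; no new data are needed. The main analysis then rests on a missing-at-random assumption, which the delta-adjusted analysis probes. This is best settled before anyone sees outcomes by arm.
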